## Abstract

**Introduction:** An unwanted consequence of population aging is the growing number of elderly at risk of neurodegenerative disorders, including dementia and macular degeneration. As nutritional and behavioral changes can delay disease progression, we designed the Walnuts and Healthy Aging (WAHA) study, a two-center, randomized, 2-year clinical trial conducted in free-living, cognitively healthy elderly men and women. Our interest in exploring the role of walnuts in maintaining cognitive and retinal health is based on extensive evidence supporting their cardio-protective and vascular health effects, which are linked to bioactive components, such as n-3 fatty acids and polyphenols.

**Methods:** The primary aim of WAHA is to examine the effects of ingesting walnuts daily for 2 years on cognitive function and retinal health, assessed with a battery of neuropsychological tests and optical coherence tomography, respectively. All participants followed their habitual diet, adding walnuts at 15% of energy (≈30–60 g/day) (walnut group) or abstaining from walnuts (control group). Secondary outcomes include changes in adiposity, blood pressure, and serum and urinary biomarkers in all participants and brain magnetic resonance imaging in a subset.

**Results:** From May 2012 to May 2014, 708 participants (mean age 69 years, 68% women) were randomized. The study ended in May 2016 with a 90% retention rate.

**Discussion:** The results of WAHA might provide high-level evidence of the benefit of regular walnut consumption in delaying the onset of age-related cognitive impairment and retinal pathology. The findings should translate into public health policy and sound recommendations to the general population (ClinicalTrials.gov identifier NCT01634841).

## Introduction

The worldwide expansion of aging populations has become a major public health challenge (Song and Chen, 2015). Increased lifespan has resulted in a steady rise of debilitating diseases related to aging, including neurodegenerative disorders, such as Alzheimer’s disease (AD), the most common type of dementia (Alzheimer’s Association, 2015), and age-related macular degeneration (AMD), the leading cause of visual loss and blindness worldwide (Lim et al., 2012). Unfortunately, to date there is no effective treatment for AD (Iqbal et al., 2014) or even mild cognitive impairment (MCI), its precursor stage (Cooper et al., 2013). Likewise, no effective preventive strategies exist for AMD, although nutritional and behavioral modifications can delay disease progression once initiated (Lim et al., 2012). In the continuum from normal cognition to MCI and dementia there is age-related cognitive decline, the onset and progression of which depends on a number of factors, including genetic variation, the level of education, environmental factors, particularly dietary habits, and the presence of cardiovascular risk factors or disease (Baumgart et al., 2015). Similar risk factors, albeit with a different genetic background, play a role in the pathophysiology of AMD (Lim et al., 2012). Optimal cognitive and visual functions are essential for quality of life and developing effective primary prevention strategies to reduce the economic and societal burden of such common age-related diseases would be of utmost public health importance.

Oxidative stress and inflammation are thought to play a pivotal role in precipitating neurodegenerative diseases, including AD (Schrag et al., 2013; Heneka et al., 2015) and AMD (Khandhadia and Lotery, 2010). Consequently, as derived from epidemiologic studies, a promising hypothesis in recent years has been that antioxidant-rich foods, such as fruit, vegetables, and particularly seeds and berries (Nooyens et al., 2011; Valls-Pedret et al., 2012; Ros and Hu, 2013; Barbour et al., 2014; O’Brien et al., 2014), and plant-based dietary patterns, especially the Mediterranean diet and the DASH (Dietary Approaches to Stop Hypertension) dietary pattern (Otaegui-Arrazola et al., 2014; Tangney et al., 2014) may protect from cognitive decline and AD. Nutrients such as n-3 polyunsaturated fatty acids (n-3 PUFA) and antioxidants, namely polyphenols, carotenoids and vitamins C and E, may have a role in preventing both cognitive impairment (Macready et al., 2009; Dangour et al., 2012; Valls-Pedret et al., 2012; Devore et al., 2013; Barnes et al., 2014; Otaegui-Arrazola et al., 2014) and macular degeneration (Age-Related Eye Disease Study Research Group, 2001; Parisi et al., 2008; Tan et al., 2009; Majumdar and Srirangam, 2010; Merle et al., 2013). Nuts in general and walnuts in particular have a rich matrix of these bioactive components and through additive effects have the potential to beneficially impact neuronal function in the brain and the retina (Poulose et al., 2014). Prospective studies have provided support for the association between nut consumption and improved cognitive performance (Valls-Pedret et al., 2012; O’Brien et al., 2014) and lower incidence of AMD (Tan et al., 2009; Amirul Islam et al., 2014). Among the different tree nuts, walnuts contain n-3 PUFA, specifically α-linolenic acid (ALA; C18:3n-3). ALA has long been believed to improve brain health indirectly via modest conversion to docosahexaenoic acid (DHA; C22:6n-3) (Domenichiello et al., 2015), which has been found to modulate brain plasticity and counteract neuroinflammation in experimental studies (Dyall, 2015). However, studies in rodents uncovered brain benefits of ALA by itself, including increased brain plasticity (Blondeau et al., 2009), reduced cell death and calcium dysregulation (Carey et al., 2013), and reduced amyloid-beta deposition (Gao et al., 2016). Other bioactive compounds in walnuts, such as arginine, tocopherols, folate, melatonin, and polyphenols also support neurological health and cognitive wellness by modulating blood pressure, HDL function, glucoregulation, endothelial vasodilator function, arterial compliance, oxidative status, and vascular inflammation (Carey et al., 2013; Del Rio et al., 2013; O’Brien et al., 2014). In support, experimental feeding studies in aged rodents have shown that walnuts improve age-related motor and cognitive deficits as assessed by rod walk, plank walk, and Morris water maze tests (Willis et al., 2009).

Easy to implement lifestyle modifications that might help prevent chronic non-communicable disorders need to be uncovered, with the concept that even small changes in the right direction can lead to substantial benefit for global health. Thus, delaying the onset of AD by only 5 years would significantly reduce its prevalence by the next decade (OECD, 2014). Thus far randomized controlled trials (RCTs) testing various interventions in patients with established AD have failed to show any benefit, probably because at this stage neuropathology is far advanced and irreversible. This underlines the need to conduct RCTs in individuals at risk but cognitively healthy, when there are little or no underlying brain changes.

Although not primarily focused on neurodegenerative disorders, one such study, the PREvención con DIeta MEDiterránea (PREDIMED) study, is a landmark RCT conducted in older individuals at high cardiovascular risk that has shown beneficial effects of Mediterranean diets supplemented with extra-virgin olive oil or mixed nuts on several age-related disorders after intervention for ∼5 years (Martínez-González et al., 2015). In the PREDIMED trial, the Mediterranean diets reduced the incidence of cardiovascular diseases by 30%, compared with a low-fat control diet, while the risk of stroke was reduced by 34% by the olive oil diet and by 49% by the nuts diet (Estruch et al., 2013). In a PREDIMED sub-study, we showed better cognitive performance associated with consumption of polyphenol-rich Mediterranean foods at baseline (Valls-Pedret et al., 2012) and cognitive improvement in participants allocated the two Mediterranean diets compared with those in the control group after 4.1 years of follow-up (Valls-Pedret et al., 2015). Thus, data from PREDIMED suggest that nuts, including walnuts, are a good option for cardiovascular and brain health. Therefore, it is reasonable to surmise that usual walnut consumption may be an effective approach to preserve cognitive abilities and visual function. However, while there is sufficient rationale for the role of walnuts in neuroprotection, direct clinical evidence is lacking. The Walnuts and Healthy Aging (WAHA) study is the first RCT assessing cognitive function and macular health in an elderly cohort following daily ingestion of walnuts for 2 years.

## Methods

### Study Design

The WAHA study is a dual center, single blind, randomized 2-year clinical trial conducted in free living, cognitively healthy elderly individuals^1^. The study is carried out in two centers: Loma Linda University, CA, USA (LLU) and Hospital Clínic, Barcelona, Spain (BCN). With a parallel design, participants were randomized to either the walnut group (consuming walnuts daily) or control group (abstaining from walnuts). Otherwise participants followed their habitual diet throughout the study. Primary aims are to assess changes in cognitive function and retinal integrity. Secondary aims relate to effects on cardio-metabolic risk factors, body weight and composition, and circulating markers of oxidation/inflammation. Additional secondary aims (BCN center) are changes in brain magnetic resonance imaging (MRI), ultrasound-assessed carotid atherosclerosis, blood pressure by 24-h ambulatory monitoring, bone mineral density, leukocyte telomere length, and microRNAs (miRNAs) related to lipoprotein metabolism.

### Participants and Eligibility Criteria

Recruitment and selection of participants took place between May 2012 and May 2014; the trial ended May 31, 2016. Participants were healthy elderly men and women with normal cognitive and visual function at the time of recruitment. Inclusion criteria were age between 63 and 79 years, apparently healthy, and equally willing to be in either of the two groups. Exclusion criteria included inability to undergo neuropsychological testing; morbid obesity (BMI ≥ 40 kg/m^2^); uncontrolled diabetes (HbA1c > 8%); uncontrolled hypertension (on-treatment blood pressure ≥ 150/100 mmHg); prior stroke, significant head trauma or brain surgery; relevant psychiatric illness; major depression; cognitive deterioration or dementia with a score < 24 on the Mini-Mental State Examination (MMSE) (Folstein et al., 1975); other neurodegenerative disorders like Parkinson’s disease; advanced AMD or eye-related conditions precluding ophthalmological evaluation; prior chemotherapy; chronic illness with projected shortened lifespan; allergy to walnuts; customary use of fish oil and/or tree nuts (> 2 servings/week) and/or other relevant sources of ALA, such as flaxseed oil or soy lecithin.

Eligible participants were recruited via mailing study brochures (LLU) or through the non-profit organization Institute of Aging (BCN), advertisements in the study centers, and word of mouth. Interested individuals attended an informational group meeting, completed a short medical questionnaire and signed the informed consent. Next candidates had a face-to-face interview with the study clinician, who assessed potential compliance, reviewed the medical history, inclusion and exclusion criteria, and recent blood work and use of medications or supplements, and administered the MMSE. Eligible participants were scheduled to have baseline tests (neuropsychological and ophthalmologic evaluations and collection of fasting blood and urine) and were then randomized to either the control or walnut group using a computerized random number table with stratification by center, sex, and age range. Couples entering the study were treated as one number and were randomized into the same group.

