### Statistical Analyses

Sample size calculation was based on prior results from the PREDIMED study (Valls-Pedret et al., 2015). We used as reference the 2-year unadjusted changes in RAVLT (total learning) scores in the Mediterranean diet enriched with nuts compared to the control diet. In order to have a 90% power to detect differences in the contrast with the null hypothesis, assuming mean changes of 1.05 and 2.10 points in the control and intervention groups, respectively, with a standard deviation of 4.00, the total number of participants required was 308 per group. Considering an estimated dropout rate of 10%, we needed to include a total of 686 participants.

All data collected in the study were entered into an online database (Onto CRF, Costaisa, Spain) managed for both centers. An oversight committee blinded to subject allocation monitored safety, quality of data collected, and trial’s progress.

Between-group differences in baseline neuropsychological and ophthalmologic data will be examined by ANOVA and further by ANCOVA adjusting for center, sex, age, education years, *APOE4* genotype, smoking, BMI, energy intake, physical activity, diabetes, hyperlipidemia, and hypertension. Changes for each individual cognitive test, cognitive composites, ophthalmologic evaluations, and foods and nutrients ensuing intervention will be assessed by ANOVA and further by ANCOVA adjusting for the variables listed above. Statistical significance will be set at the *P* < 0.05 level. Analyses will be performed using SPSS software, version 16.0 (IBM Corp., New York, NY, USA).

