**FIGURE 2 F2:**
[figure not shown]
**Recruitment and participant allocation**.

The baseline characteristics of the study participants by group are provided in **Table 2**. The mean age was 69.1 years and 67.9% were women. The characteristics of participants in the two intervention groups were well balanced except for smoking status, as there were more current smokers in the walnut group than in the control group.

**Table 2 T2:** Baseline characteristics of 708 WAHA participants by treatment allocation.

Characteristics	Walnut	Control	*P*-value^∗^
No. (%)	362 (51.1)	346 (48.9)	
Enter with partner – no. (%)	98 (27.1)	88 (25.4)	0.62
Women – no. (%)	244 (67.4)	237 (68.5)	0.76
Age – year (mean ± SD)	69.4 ± 3.8	68.9 ± 3.5	0.07
Smoking – no. (%)			0.02
Never smoker	303 (83.7)	293 (84.7)	
Former smoker	43 (11.9)	49 (14.2)	
Current smoker	16 (4.4)	4 (1.2)	
Education – no. (%)			0.83
Basic (0–4 years)	11 (3.0)	8 (2.3)	
Elementary (5–8 years)	60 (16.6)	65 (18.8)	
Secondary (9–12 years)	70 (19.3)	65 (18.8)	
Post-secondary (>12 years)	221 (61.0)	208 (60.1)	
Height – cm	164.3 ± 9.5	163.3 ± 9.0	0.14
Weight – kg	73.8 ± 15.2	73.5 ± 14.7	0.78
Body mass index – kg/m^2^	27.2 ± 4.3	27.5 ± 4.4	0.42
Hypertension – no. (%)	191 (52.8)	183 (52.9)	0.97
Type-2 diabetes – no. (%)	37 (10.2)	33 (9.5)	0.76
Dyslipidemia – no. (%)	203 (56.1)	182 (52.6)	0.35

*Data are no. (%) or mean ± SD, as appropriate.*

*^∗^Obtained by Chi-square test or ANOVA, as appropriate.*

To objectively determine adherence to supplemental walnuts, we measured the RBC proportions of ALA, a fatty acid characteristic of walnuts, at baseline and after 1 year of intervention in a random sub-sample of participants. There were no significant differences in RBC ALA between intervention groups at baseline (**Figure 3A**). After adjusting for center, age, and sex, 1-year changes in RBC ALA were increases of 0.16% of total fatty acids (95% confidence interval, 0.144–0.183) and 0.02% (95% confidence interval, 0.001–0.039) for the walnuts and control group, respectively (*P* between groups < 0.001) (**Figure 3B**).

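### Couples are randomised as one unit, but the ANOVA/ANCOVA planned for both primary outcomes treats partners as independent; the effect is small and depends on an ICC the article does not give

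*Protocol article*

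**What the plan says.** Three places in the protocol article bear on this.

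- **Participants and Eligibility Criteria.** Randomisation is stratified by centre, sex and age range, with one exception to individual allocation: "Couples entering the study were treated as one number and were randomized into the same group".
- **Table 2 (Anticipated Results).** The row "Enter with partner" gives 98 (27.1%) of 362 in the walnut group and 88 (25.4%) of 346 in the control group. The percentages use participants, not couples, as the denominator.
- **Statistical Analyses.** Changes in individual cognitive tests, cognitive composites, "ophthalmologic evaluations, and foods and nutrients ensuing intervention will be assessed by ANOVA and further by ANCOVA adjusting for the variables listed above". The covariate list is explicit: "adjusting for center, sex, age, education years, *APOE4* genotype, smoking, BMI, energy intake, physical activity, diabetes, hyperlipidemia, and hypertension". It has no couple or household term, and the section names no mixed model, GEE or cluster-robust variance. The sample size paragraph has no design effect.

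The two primary outcomes in the Outcomes section, the global cognitive composite and the average retinal nerve fiber layer thickness, both fall under this analysis.

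**The concern.** For about a quarter of participants the unit of randomisation is the pair, while the unit of analysis is the person. ANOVA and ANCOVA estimate the standard error of the group difference as if all participants were independent. Because partners always share an arm, any positive correlation between their outcomes adds to the variance of the between-group contrast, and the naive standard error misses this addition. Confidence intervals are then too narrow, and a test at P < 0.05 rejects a true null hypothesis more than 5% of the time.

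Adjusting for centre, age, BMI and the rest may absorb part of what partners have in common, but it does not model the remaining correlation. Some correlation is plausible. The Intervention section provides extra walnuts for family needs and restricts certain cooking oils, and both act at household level. The argument is strongest for foods and nutrients and weaker for two-year change in cognition or retinal thickness.

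What is at stake is the validity of the P values and intervals, chiefly for a borderline primary result.

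**Working it through.** **Inputs from the article.** Difference in mean change 2.10 − 1.05 = 1.05 points on RAVLT total learning; SD 4.00; 308 per group; 90% power; 10% dropout; significance level 0.05 (taken as two-sided, since one-sided would need only 249 per group). Participants with a partner: 98 + 88 = 186 of 708. Completers: 362 − 38 = 324 walnut and 346 − 34 = 312 control, 636 in all.

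**Assumed.** The within-couple ICC of the change score is not given; 0.1 to 0.5 is shown, with 1.0 as the limit. Both partners are taken to be enrolled and analysed.

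**Step 1: reproduce the plan's figure under independence.**

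n per group = 2 × [4.00 × (1.960 + 1.282) / 1.05]² = 305, against 308 stated.

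Power at 308 = Φ(1.05 / (4.00 × √(2/308)) − 1.960) = 90.3%.

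Dropout: 308 / 0.90 = 342.2, rounded up to 343 per group, or 686 in total, as stated.

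The stated size therefore contains no allowance for couples.

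**Step 2: design effect.** With clusters of one or two, and a fraction f of participants in pairs:

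f = 186/708 = 0.263; DE = 1 + f × ICC.

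This corresponds to 93 couples and 522 singles, or 615 randomised units.

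**Step 3: consequences.**

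- Ratio of correct to naive standard error = √DE
- Actual type I error of the naive test = 2 × [1 − Φ(1.960/√DE)]
- Power at 308 per group = Φ(1.05 / (4.00 × √(2 × DE/308)) − 1.960)
- Power with the 324 + 312 completers uses arm-specific design effects (f = 0.271 and 0.254)

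| Assumed ICC | DE | SE ratio | Type I error | Power, 308 per group | Power, 636 completers |
|---|---|---|---|---|---|
| 0 | 1.000 | 1.000 | 5.0% | 90.3% | 91.1% |
| 0.1 | 1.026 | 1.013 | 5.3% | 89.5% | 90.4% |
| 0.2 | 1.053 | 1.026 | 5.6% | 88.8% | 89.7% |
| 0.3 | 1.079 | 1.039 | 5.9% | 88.0% | 89.0% |
| 0.5 | 1.131 | 1.064 | 6.5% | 86.5% | 87.5% |
| 1.0 (limit) | 1.263 | 1.124 | 8.1% | 82.6% | 83.8% |

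At 308 per group, power stays within two points of 90% up to an ICC of about 0.30. With the 636 completers it stays at or above 90% up to about 0.16.

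**The case against.** The strongest reply is that this is nearly harmless. Clusters have at most two members and hold only a quarter of the participants, so even perfect correlation gives a type I error of about 8%. The relevant ICC is that of residual two-year change after adjustment for centre, age, education, smoking, BMI and activity, traits that partners may share, so it could be well below 0.3 for cognition or retinal thickness. Walnut sachets were sized to the individual, and only the extra allowance was for the family. If one partner drops out, the paired fraction falls. All of this stands, and it limits the size of the problem.

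A second reply is that the article condenses a fuller plan, which could add a couple term. That is possible, but the article is not silent here: it names the method and lists the covariates, and the method as stated assumes an independence that the randomisation rule contradicts.

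A reader might also infer more than the article supports:

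- **That the trial is underpowered, or the stated 90% materially wrong.** The loss is one to two points up to an ICC of about 0.30, and more people completed (636) than were planned (616). The 90% also refers to RAVLT total learning, not to either primary outcome.
- **That every outcome is affected.** Statistical Analyses assigns ANOVA/ANCOVA to cognitive, ophthalmologic and dietary variables. It names no method for incident MCI or AD, MRI, carotid, bone or blood pressure outcomes.
- **That standard errors are certainly too small.** This needs a positive ICC, which is plausible but not documented.

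**Conclusion.** The mismatch between unit of randomisation and unit of analysis is real and reaches both primary outcomes. Its consequence is conditional and small. For an assumed ICC of 0.1 to 0.3, the correct standard error exceeds the naive one by 1.3% to 3.9% and type I error is 5.3% to 5.9%; at 0.5 the figures are 6.4% and 6.5%. These results rest on a positive ICC that the article does not give, on 93 intact couples inferred from Table 2, and on large-sample normal formulas. The sample size needs no change. This should be fixed because the error is in a stated rule and a borderline P value could turn on it, but it does not undermine the design.

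**What to change.** For the outcomes that Statistical Analyses assigns to ANOVA/ANCOVA, fit the same model with a random intercept for the randomised unit (the couple, or a single participant as a cluster of one). Alternatively, keep the ANCOVA and use cluster-robust standard errors on that unit. Report the estimated ICC for each primary outcome, and add one sentence saying that couples were allocated together and how the analysis allows for it.

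The cost is one model term and, if the ICC is positive, slightly wider confidence intervals. Entry with a partner is already recorded, so no new data are needed beyond a couple identifier linking the two records.

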### Intervention

Participants received 15% of daily energy intake as walnuts for 2 years or abstained from walnuts. To estimate the required amount of walnuts, participants completed a 3-day diet history and a physical activity questionnaire at baseline. The physical activity factor and the energy requirements were obtained using the World Health Organization formula for energy needs for adults > 60 years (World Health Organization, 1985). The estimated amount of walnuts ranged from 1 to 2 oz/day (≈30–60 g/day). Sachets for daily consumption containing 30, 45, or 60 g of raw, pieced walnuts were provided as 8-week allotments to the participants in the walnut group at the time of their 2-monthly clinic visits with the dietitians. Instructions were given to eat walnuts daily, preferably as the raw product, either as a snack or by incorporating them into shakes, yogurts, cereals, or salads. To improve participants’ compliance, 1-kg extra walnut allowances were provided every 2 months to take into account family needs. Participants in the control group were advised to abstain from eating walnuts for the duration of the study. Use of ALA-rich canola and soybean oils was restricted.

Once randomized, participants were scheduled for 2-month visits with the study dietitians aimed at assessing compliance, increasing retention, and collecting data on diet adherence, medication changes, anthropometry, and clinical blood pressure. For the walnut group participants, the dietitians noted any side effects and collected used walnut sachets as a measure of compliance. The rapport built by the dietitians with the participant during the periodic scheduled visits was critical to retain them for the entire length of study. Since participants in the control group had no active intervention, to improve retention, quarterly educational group activities unrelated to the study were offered to them.

